## Discussion

Our study set out to investigate the utilization of a new and interdisciplinary model of care at the interface of occupational and psychosomatic medicine. The main objective is to identify different types of patients with specific combinations of traits with regard to the setting (outpatient clinics vs. workplace). A pre-post test 12 weeks after consultation will detect changes in ability to work, disease severity and quality of life compared with the first consultation. We will describe the extent to which psychotherapeutic recommendations have been followed by the patients. Furthermore, we evaluate patient satisfaction. Using the instrument of qualitative interviews we want to work out the appraisals, attitudes, and experiences of employees, occupational physicians, therapists and other company personnel with this new model of care.

### Strengths and weaknesses

The main strength of our study is that, except for one non-empirical article [11], there is little data in this field. We will evaluate whether or not we will reach different types of patients if we, as health professionals, initially see patients at their workplace and not within the traditional setting of a psychosomatic outpatient clinic. The best way to investigate this question is an explorative design with consecutive recruitment of patients. Therefore, we do not match groups for age, gender or desease severity.

A disadvantage of the explorative design is the inability to compute effect sizes. To be able to obtain utilization data of our model under routine conditions, we decided to choose a non-randomized controlled design. Another limitation of the study is the recruitment of a sample size of 280 participants in the allotted time of 10 months. Most studies in this field have problems recruiting participants. In contrast to the other studies, however, we expect a high rate of participation because the "psychosomatic consultation in the workplace" has been appreciated and well-received by the employees so far. In addition, the employees are assured that the collected data will be kept confidential under the supervision of the research group at the university. Another critical issue might be a high dropout rate at follow-up which we will attempt to minimize with a reminder phone call, email or letter. A long-term follow-up survey (i.e. at 6 months after T1) would be reasonable, but cannot be realized within the funding period. We plan to investigate this issue in a future project.

### Relevance of the study

A lack of easy accessability, as well as stigmatisation of the mental health care system [26], obstructs help-seeking behavior. In Germany, 50% - 90% of individuals with psychosomatic disorders do not manage to obtain professional care, as a recent report on behalf of the National Association of Statutory Health Insurance Physicians (KBV) revealed [27,28]. These aspects, among others, may contribute to the chronification of common mental disorders such as depression, anxiety and adjustment disorder, as well as functional somatic disorders. Therefore, common mental disorders should be treated within the early stages of onset, as they are known to be especially responsive to treatment during the early phases of illness [29]. In addition, a recent study showed that even if the employees’ home life is stressful, tackling workplace stress is likely to improve employees’ psychological health [30]. These facts validate the need for brief, easily accessible and tailored interventions at the workplace.

With the model “psychosomatic consultation in the workplace,” we aim to offer an integrative, timely and easily accessible first consultation to affected employees. The stigma of mental disorder is intended to be minimized by bringing the psychosomatic consultant to the patient instead of vice versa. Furthermore, the psychosomatic consultation is embedded within occupational health facilities at the workplace. These aspects are likely to make the consultation at the workplace an instrument to reduce chronification.

In this study, we will describe the utilizers of a new model of mental health care in the workplace. This model follows numerous other concepts of work-related programs, such as return to work interventions [31,32], stress prevention training [9,33,34] and interventions for healthy management [35,36]. “Psychosomatic consultation in the workplace” addresses those workers and employees who still have the ability to go to work. It focuses on improving work ability of affected individuals, and hence, can be regarded as a form of secondary and tertiary prevention.

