## Abstract

**Background:**

Mental health issues are gaining in importance in society and the economic system. At the same time, the accessibility and stigmatisation of the mental health care system in Germany can obstruct help-seeking behavior and delay early psychotherapeutic interventions. Therefore, new models of care are being established at the interface of company-supported health promotion and conventional health insurance sponsored outpatient care for people developing mental illnesses. Two large industrial companies, in cooperation with two psychosomatic clinics, have recently established a model of “psychosomatic consultation in the workplace“. This new model of care offers the opportunity for a first psychotherapeutic door to door consultation with occupational medicine within the industrial workplace. The main empirical goals of this study are:

1) Describing the differences between patients who use this new diagnostic and therapeutic offer within the industrial workplace vs. patients who visit a conventional regional outpatient clinic, especially in regard to symptom duration and severity, work ability, and demographic characteristics, and

2) A first evaluation of how patients may benefit more from this new model of care compared to those first seen by standard outpatient care.

In the qualitative part of the study, occupational physicians, psychosomatic therapists, involved personnel and select employees of the involved companies will be asked to comment on their experiences with this new approach.

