Currently, little is known about the profile of utilizers, or about the effects of this new model of care. Therefore, our study aims to assess the following research questions:

1. Are there differences in demographic, clinical and psychometric characteristics between patients who use the consultation offer in the workplace versus patients who use conventional outpatient care? Is this new model of mental health care successful in reaching employees suffering from psychological disorders earlier in the course of their illness, compared to patients who seek help in conventional outpatient care?

2. What changes occur within a three-month follow-up period after using the offer "psychosomatic consultation at the workplace"? Are they different from those of a conventional outpatient clinic?

3. What is the feedback (i.e. appraisals, attitudes, criticism) of persons who are involved with the offer "psychosomatic consultation in the workplace"?

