### Instruments and selected items used in the quantitative analysis

The questionnaires at T1 and T2 are both structured into five sections.

At both time points, we will examine the nature and severity of mental illness through self administered instruments resulting in discrete sumscores or subscale sumscores: the Patient Health Questionnaire (PHQ) [15], health-related quality of life (Short-Form 12, SF-12) [16], ability to work (work ability index, WAI) [14], burnout syndrome based on work-related stress (Maslach Burnout Inventory, MBI) [17], cognitive and emotional irritation (irritation scale, IS) [18] and working conditions (using the short questionnaire for work analysis, KFZA [19]).

At T1 we ask for demographic variables (age, gender, marital status, number of own children and the number of children in a household, educational and occupational status) as well as the number of previous contacts with the mental health care/psychotherapeutic system. The nature and frequency of previous psychotherapeutic treatments will be specified in months and standardized. The duration of the chief complaint will be recorded by the interviewer and also expressed in months.

The questionnaire of T2 has additional questions about the follow-up of the patient in the psychotherapeutic system, the implementation of the follow-up recommendations and patient satisfaction (ZUF-8) [20] (Table 1).

**Table 1 T1:** Target assessments and instruments

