### Statistical analysis

Research question 1 : *Are there differences in demographic, clinical and psychometric characteristics between patients who use the consultation offer in the workplace* versus *patients who use the established outpatient care?*

The differences between treatment groups will be examined by means of logistic regression analysis (in the form of binomial and multinomial models) including age, sex, educational level, occupational category, using the number of previous contacts with psychiatric-psychosomatic services as independent variables. The results of the logistic regression models will be used to estimate the propensity scores for the conditional probability of being referred to a particular treatment group.

The factors of interest of research question 1 are the type and severity of the disease (PHQ) the duration of symptoms, the health-related quality of life (SF-12), work ability (WAI), work-related stress effects (MBI, IS), work requirements (KFZA), the number of previous contacts with the mental health care system as well as demographic factors (Table 1). The demographics may be incorporated to the model independently or in terms of propensity scores.

By using multivariate analysis (latent class analysis = LCA) techniques it is possible to discern which patients with specific combinations of traits fit into certain clusters and determine the effect the particular setting has on the patients’ assignment in each particular cluster. The multivariate analysis is performed using the General Mixture Model (GMM) approach [21,22]. The basis here is the relationship between various characteristics of a limited number of categorical latent classes. The number of latent classes can be determined via various statistical methods (Bayesian Information Criterion, Akaike Information Criterion, Lo-Mendel-Rubin Test). By extending this model to a conditional latent class model, the effects of covariates on the likelihood of class membership can be estimated. The covariates in this study are the respective treatment settings, demographic data and job-specific characteristics of the responders.

Research question 2: *What are the changes 12 weeks after initially using the offer "psychosomatic consultation in the workplace" and how are they different from those in the control group?*

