### Inclusion criteria

The only inclusion criterion is that the respondents must be at least 18 years of age. Other inclusion criteria are not relevant since we are recruiting consecutively and this is an explorative study.

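### A difference in work ability between settings may partly restate whom the workplace offer is aimed at, because at-work status is not among the listed adjustment variables

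*Protocol article*

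**What the plan says.** Under Relevance of the study, the protocol article states that the offer "addresses those workers and employees who still have the ability to go to work". Under Inclusion criteria, the rule for all four settings is: "The only inclusion criterion is that the respondents must be at least 18 years of age".

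The abstract announces a comparison of the two kinds of patients "especially in regard to symptom duration and severity, work ability, and demographic characteristics". The Statistical analysis section lists among the factors of interest for research question 1 "work ability (WAI), work-related stress effects (MBI, IS), work requirements (KFZA"), together with PHQ, symptom duration, SF-12 and demographics. The second half of research question 1 is evaluative: "Is this new model of mental health care successful in reaching employees suffering from psychological disorders earlier in the course of their illness", compared with conventional outpatient care.

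WAI is also the primary outcome of research question 2 and the variable used in the power calculation. For research question 2, the effect of setting on change is estimated by linear regression with propensity scores. These come from logistic models "including age, sex, educational level, occupational category, using the number of previous contacts with psychiatric-psychosomatic services as independent variables". The T1 demographic items are given as "age, gender, marital status, number of own children and the number of children in a household, educational and occupational status".

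**The concern.** One arm is described by a property, still being able to go to work, that lies close to what WAI measures. The other arm carries no such description. If employees on sick leave attend the clinics more often than the workplace consultation, mean WAI at T1 will be higher at the workplace, even if patients who are at work have the same WAI in both settings.

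Two readings are at stake. At T1, a better WAI at the workplace could be cited as evidence that the model reaches people sooner, although it may only show whom the offer is aimed at. At T2, some of the change in WAI among clinic patients could come from people returning to work, or failing to, and the regression would attribute this to setting. The article does not determine the direction of that second effect.

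Age, sex, education, occupational category and previous contacts do not separate an employee at work from one on sick leave. Restricting the clinics to employed patients does not help, because a sick-listed employee is still employed.

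**Working it through.** **What the texts establish**

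- Workplace arm: a stated target group of people still able to go to work (Relevance of the study).
- Clinic arm: adults, with no rule on employment or sick leave (Inclusion criteria).
- Outcome affected: WAI, at T1 for research question 1 and as change to T2 for research question 2.
- Adjustment: five listed variables, none of which is at-work status (Statistical analysis).
- Unmatched, non-randomised design: acknowledged under Strengths and weaknesses. The consequence of the target group for WAI is not mentioned there.

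**Yardstick from the article**

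The article gives no figure for the share on sick leave or for their WAI, so there is no stated result to reproduce. The only yardstick is the planning assumption that setting explains 5% of the variance. With equal groups:

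- f² = 0.05 / (1 − 0.05) = 0.0526
- d = 2 × √0.0526 = 0.46 SD

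**Illustration on assumed inputs**

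Let p be the share of clinic patients on sick leave (assumed 10-50%) and g their WAI deficit in SD units (assumed 0.5-1.5). Suppose that all workplace patients are at work, that patients at work have the same WAI in both settings, and that the SD is 1 within each stratum.

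- Raw gap = p × g
- Clinic variance = 1 + p(1 − p)g²; averaged over two equal arms, 1 + p(1 − p)g²/2
- Standardised gap d = p·g / √(1 + p(1 − p)g²/2)
- Share of variance = d² / (d² + 4)

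Example with p = 0.3 and g = 1: 0.3 / √(1 + 0.21/2) = 0.3 / √1.105 = 0.29 SD, or 2.0% of variance.

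| Share sick-listed | g = 0.5 | g = 1 | g = 1.5 |
|---|---|---|---|
| 10% | 0.05 SD (0.06%) | 0.10 SD (0.24%) | 0.14 SD (0.51%) |
| 20% | 0.10 SD (0.24%) | 0.19 SD (0.92%) | 0.28 SD (1.87%) |
| 30% | 0.15 SD (0.55%) | 0.29 SD (2.00%) | 0.40 SD (3.93%) |
| 40% | 0.20 SD (0.96%) | 0.38 SD (3.45%) | 0.53 SD (6.62%) |
| 50% | 0.25 SD (1.49%) | 0.47 SD (5.26%) | 0.66 SD (9.89%) |

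The range is 0.05 to 0.66 SD, from negligible to somewhat above the planning effect.

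**Two checks on the reasoning**

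- Restriction to employed clinic patients: p becomes the share sick-listed among the employed. The formula is unchanged, and the gap disappears only if p = 0.
- Sick-listed employees in the workplace arm too: the raw gap becomes (p clinic − p workplace) × g. With 30% against 10% and g = 1 it is 0.20 SD; with equal shares it is zero. The concern depends on unequal shares, which the data can show only if the status is recorded.

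**The case against.** The strongest reply is that research question 1 asks who uses each setting. The Discussion gives identifying different types of patients as the main objective, and matching is declined on purpose. A WAI gap that arises from whom the offer reaches is then part of the answer. This stands for the descriptive half of the question, and it is why the comparison of all users should remain primary. It does not cover the reading of WAI as a sign of earlier reach, nor the setting effect in research question 2.

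It can also be said that limiting the comparison to patients at work may remove the effect of interest. If the model reaches employees sooner, one consequence would be that they are seen before they are sick-listed. This stands, and it rules out replacing the main comparison with an at-work one. The article also has a direct measure of earlier reach: duration of the chief complaint in months, recorded at T1.

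A reader might infer more than the article supports in four places:

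- **That being at work is an entry rule for the workplace arm.** The sentence describes a target group. Neither the inclusion criterion nor the description of access (referral by occupational physicians or the social worker in Stuttgart, direct access in Ulm) bars a sick-listed employee.
- **That the article says clinics see employees on sick leave.** It does not; this is inferred from the open eligibility.
- **That a severity difference (PHQ, SF-12) is built in.** Being able to go to work is no ceiling on symptoms, and the Background describes the need as extending to established mental illness.
- **That sick leave is not recorded.** The article summarises its items and does not list the seven WAI questions, so the full questionnaire may contain it. What the article does fix is the list of propensity variables.

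Finally, 0.46 SD is only a rough yardstick. The power calculation concerns WAI as the primary outcome, which the article places at T2. The numbers for research question 1 are said to follow from schedule and feasibility.

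**Conclusion.** The point holds as a limit on how WAI differences can be interpreted. The described target group of one arm, the age-only restriction of the other and the listed propensity variables together leave setting partly confounded with at-work status, so far as the shares on sick leave differ between settings. A T1 WAI difference may partly restate whom the offer is aimed at, and the T2 comparison may mix setting with return to work.

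The article cannot settle the size. The range in the table rests wholly on the assumed shares and deficits, and on all workplace patients being at work. The result does not show that the study will find a spurious effect, nor that the descriptive comparison of users is wrong.

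**What to change.** 1. Record at T1, in all four settings, whether the patient is currently at work or on sick leave, unless the questionnaire already contains this.
2. Keep the comparison of all users as the primary analysis for research question 1, and show T1 WAI by setting and at-work status as a supplement.
3. For research question 2, add at-work status to the propensity model or enter it as a covariate in the WAI regression. Add a sensitivity analysis limited to patients at work at T1 in both settings.
4. State that earlier reach is judged on duration of symptoms and not on WAI.
5. Add a sentence to the limitations saying that the offer's target group may contribute to a difference in work ability.

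The cost is one yes/no item and two additional analyses. The at-work comparison uses fewer clinic patients, so its interval will be wider. It may also condition on a consequence of earlier reach, which is why it supplements the main comparison and does not replace it.

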## Abbreviations

DP: Depersonalization; DSM IV: Diagnostic and Statistical Manual of Mental Disorders 4th edition; EE: Emotional Exhaustion; ICC: Intraclass Correlation; ICD-10: International Classification of Diseases and Related Health Problems, 10th edition; IS: Irritation Scale; KBV: National Association of Statutory Health Insurance Physicians; KFZA: Short Questionnaire for Work Analysis; LAU: Location as Usual; MBI: Maslach Burnout Inventory; PA: personal accomplishment; PHQ: Patient Health Questionnaire; SF-12: Short Form 12; T1: Timepoint 1, baseline; T2: Timepoint 2, follow up; WAI: Work Ability Index; ZUF-8: Patient Satisfaction Scale, 8 Items.
